### Study intervention

Study participants will be randomly assigned to receive a histamine-2 receptor antagonist (i.e., ranitidine or famotidine) or placebo. As there are no pediatric-specific recommendations regarding type of SUP, we elected to conduct our study with a histamine-2 receptor antagonist since this is the current standard practice at our institution. In this pragmatic design, participants can receive study drug either intravenously or enterally, depending on the clinician’s preference. The dosing is based on age and route. For ranitidine, neonates (< 31 days old) will receive either 1 mg/kg intravenously/enterally every 12 h, and infants (≥ 31 days old) will receive 1 mg/kg intravenously/enterally every 8 h. For famotidine, if the participant is < 3 months, they will receive 0.5 mg/kg/dose IV/PO daily, and if > 3 months old, they will receive 0.25 mg/kg/dose IV every 12 h or 0.5 mg/kg/dose PO every 12 h. As part of pharmacovigilance, surveillance for hepatic dysfunction and thrombocytopenia will be included in the case report forms.

The placebo will be in an equivalent volume of 0.9% saline intravenously or a stevioside sugar-free syrup vehicle that resembles the color, tonicity, and texture of oral ranitidine or famotidine. Individualized unit-dose syringes will be provided to each study participant and blinded to the study team, bedside clinicians, parents, and outcome assessors. All interventions other than the study drug are left to the discretion of the treating clinicians. Once a participant completes the study, the clinicians can prescribe acid suppression per their usual practice. Adherence to intervention protocols is monitored daily by research staff by checking in with participant’s bedside nurse to ensure medication administration and timely sample collection. The research staff also speaks with the attending physician daily to assess for any adverse events or study-related issues. Patients with hemodynamically significant UGI bleeding will be withdrawn from the study, as they would likely require open-label acid suppression. There also exist study-halting criteria, which would stop the study until the DSMB reviewed and recommended continuation of the study. Final determination of trial termination will be made by principal investigators, if necessary. Auditing of trial conduct is done every 6 months by the DSMB, independent of the investigators and sponsor. The study-halting criteria include a total of 3 UGI bleeding events or an enrollment number of less than 20 patients per year. The principal investigators will have access to the final trial dataset.

### Measurements and definitions

Data will be imported into a secure, password-protected, FDA-compliant database (InForm® Electronic Data Capture). Data collection will include demographic, procedural, laboratory, pharmaceutical, nutritional, ventilatory, and outcome variables. Samples obtained will include oral swabs, gastric aspirates (via indwelling NG tube), discarded blood, and urine at the initiation and conclusion of the study. In addition, serial stool samples will be collected while on study. Data are collected in daily case report forms (CRFs) and then imported weekly into the InForm ITM (Integrated Trial Management) System. Monthly audits of the InForm database are completed with the study investigators to ensure completeness and minimize transcription errors. In addition, the InForm database has safety metrics built in for out of bounds values.

Important definitions include the following:
Clinically significant UGI bleed—new-onset bleeding from the UGI tract (i.e., hematemesis, bloody gastric aspirate, or hematochezia) AND associated with (a) decrease in hemoglobin by 2 g/dL, OR (b) decline in mean arterial blood pressure by 10 mmHg or initiation/increase of inotrope/vasoactive medications, OR (c) increase in heart rate by 20 beats per minute in the absence of an arrhythmia or fever, OR (d) need for unanticipated blood transfusion, OR (e) unexpected endoscopic or operative procedure to achieve hemostasis. This definition has been used in adult randomized controlled trials with excellent inter-rater agreement [15, 16].Bloodstream infection (BSI)—a laboratory-confirmed bloodstream infection with or without a central line in place.Ventilator-associated event (VAE)—a deterioration in respiratory status after a period of stability or improvement on the ventilator, evidence of infection or inflammation and laboratory evidence of a respiratory infection (CDC).Urinary tract infection—a laboratory-confirmed urinary tract infection with or without a urinary catheter in place.*Clostridium difficile* associated diarrhea—diarrhea in the presence of a positive *C. difficile* test.Mediastinitis—a laboratory-confirmed organism from mediastinal tissue or fluid, or based on gross anatomic exam, or has hyper/hypothermia or apnea or bradycardia or sternal instability with at least one of the following: (a) purulent drainage from the mediastinal area or (b) mediastinal widening on imaging (CDC).Superficial wound infection—has two of the following symptoms: (a) erythema, (b) tenderness, (c) swelling AND a laboratory-confirmed organism is identified from the wound.Gastrointestinal microbiota—difference in oral and stool microbiome between the 2 groups in this study will be examined.

### Sample analyses

For assessment of stool microbiota, sequence-based microbial community surveys of stool samples will be carried out by 16S rRNA gene-based sequencing in the Microbial Genomics and Transcriptomics Core at the Broad Institute. Their protocol targets the V4 window of the 16S rRNA gene and uses Illumina MiSeq system at the Broad Genomics Platform to produce on average 25,000 quality filtered, stitched paired-end reads per sample, representing the current state-of-the-art [17]. In addition, a higher resolution community survey and complementary functional survey of a subset of the stool samples (20%) will be obtained using metagenomic shotgun DNA sequencing, to be performed at the Broad Institute in the Broad Technology Labs and Genomics Platform. Metagenomic libraries will be constructed using the Nextera XT DNA library preparation kit (Illumina) and sequencing will be performed on an Illumina HiSeq 2000 to generate a minimum of 2 Gb of 101 nt paired-end reads.

For evaluation of oral and gastric microbiota, samples will be subjected to ribosomal DNA (rDNA) amplicon sequencing to characterize the composition of these microbiome communities. First, DNA will be extracted using a robust commercial extraction kit. Next, rDNA hypervariable regions of specific kingdoms will be amplified using universal primers. For bacteria, 16S V3V4 will be targeted using 5′-CCTACGGGNGGCWGCAG-3′ and 5′-GGACTACNVGGGTWTCTAAT-3′; for fungi, ITS1 is targeted using 5′-CTYGGTCATTTAGAGGAAGTAA-3′ and 5′-GCTGCGTTCTTCATCGATGC-3′. Specifically, Illumina adapter sequences and variable spacers are added 5′ upstream of these sequences to enable high-throughput multiplexed sequencing. The prepared amplicons will then be pooled and sequenced using Illumina Miseq 2 × 300 bp platform. Illumina raw reads will be de-multiplexed, quality trimmed, dereplicated and denoised, and finally mapped against established rDNA databases. The derived OTU table will document the relative abundance of each taxonomy within each sample.

### Outcomes

The central objective for our pilot study is to investigate whether a clinical trial assessing the safety and efficacy of withholding SUP in infants with CHD in the cardiac ICU is feasible. The trial will be considered feasible if each of the following 4 a priori variables are met: (1) > 80% of eligible patients are approached for consent (*screening*), (2) > 20% of eligible patients are randomized (*enrollment and consent*), (3) > 80% of consented patients received their first dose of study drug within 48 h (*allocation*), and (4) > 80% protocol compliance achieved (*protocol adherence*). Adherence to the protocol is defined as having received all doses of study drug as prescribed during the study period. Protocol deviation is defined as either premature termination of the study or prescription of SUP that is not part of the study while enrolled. In addition to feasibility, we will assess safety by comparing the difference in the incidence of clinically significant UGI bleeding and hospital-acquired infections between participants receiving SUP versus placebo. Finally, we will explore the changes to the gut microbiota by comparing the absolute and serial differences in the abundance of bacteria and functional microbial profiles between those receiving SUP compared to placebo. The study investigators will not be blinded to primary outcome measures. The microbiome specimens (for secondary outcome measure) will be processed and analyzed without revealing their study group allocation and thus will be blinded.

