### Recruitment and study flow

Potential patients will be screened for eligibility, and one of the principal investigators will approach the family of an eligible patient for written consent. If the legal guardian grants consent, the patient will be enrolled in the study and then randomized to one of two arms. Please see consent form in Supplementary files. Study procedures will be continued until the patient (1) no longer requires respiratory support for greater than 24 h, (2) transfers to the floor or is discharged from the cardiac ICU, (3) completes 14 days of study drug, or (4) at any time during the study the primary provider believes that open-label acid suppression is indicated (Fig. 1). To ensure adequate enrollment and retention, we will provide education of the study objectives and procedures to important subspecialist groups, send mailers to eligible patients prior to delivery or surgery, and post signs about the study in the cardiac intensive care unit and preoperative clinic.

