### Sample size

We powered the precision of our feasibility estimates for both screening and drug initiation—which we deemed as the two most important feasibility measures. There are approximately 600 patients under 1 year of age admitted to the cardiac ICU each year, and we anticipate that an estimated 200 patients will be eligible over the 2-year recruitment period. The target to demonstrate feasibility is screening 80% of all patients. If *n* = 600, the lower limit of the 95% one-sided confidence interval will include 80% as long as the observed screening rate is at least 82.7%. There are 100 patients to be randomized in this pilot trial. The target to demonstrate feasibility with respect to drug initiation is to have 80% of randomized patients receive their first dose of study drug within 48 h. With *n* = 100, the lower limit of the 95% one-sided confidence interval will include 80% as long as the observed drug initiation rate is at least 86.9%. That is, as long as the observed drug initiation rate is at least 86.9%, we can be 95% confident that the drug initiation rate, to be realized in a future trial, is at least 80%. The study is not powered to assess a statistical difference between the incidence of UGI bleeding and hospital-acquired infections, as the historical incidences are very low, 0.5% and 2%, respectively. These outcomes will be further assessed in a future larger, multicenter trial.

For the assessment of oral, gastric, and stool microbiota, a total of 600 samples (2 samples per site) will be obtained from the 100 patients. We estimate detectable effect sizes using these sample sizes based on the Human Microbiome Project [14]. With adjustment for three covariates: one categorical binary (antibiotics), one continuous (age), and one categorical tertiary (hospital-acquired infections), we anticipate a power of 0.9 to detect a 1.36% level of rare taxon relative abundance and a 3.46% level of common taxa relative abundance, within a treatment arm between two time points, and similarly between two treatment arms at a given time point for either oral, gastric, or stool samples. All estimates incorporate stringent Bonferroni multiple-hypothesis correction to an adjusted *p* value of 0.05. Approximating as above, the corresponding detection limit for 250 metagenomic pathways with power of 0.9 would be 3.87%.

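### The 48 h first-dose feasibility criterion is sized on randomized patients but decided on consented patients

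*Protocol article*

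**What the plan says.** The criterion appears twice in the protocol article, with two denominators.

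- **Sample size:** the target is that "80% of randomized patients receive their first dose of study drug within 48 h". The n is fixed by "There are 100 patients to be randomized in this pilot trial". The precision statement is "lower limit of the 95% one-sided confidence interval will include 80% as long as the observed drug initiation rate is at least 86.9" per cent, and the section concludes from it that a future trial's initiation rate would be at least 80%, with 95% confidence.
- **Outcomes:** criterion 3 is that "> 80% of consented patients received their first dose of study drug within 48 h". The decision rule is "The trial will be considered feasible if each of the following 4 a priori variables are met", so missing criterion 3 alone makes the trial not feasible. In the same list, criterion 2 counts patients who are randomized.

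The order of events is given under Recruitment and study flow: "If the legal guardian grants consent, the patient will be enrolled in the study and then randomized to one of two arms". Table 1 marks informed consent under both the pre-study column and study day 1, and marks allocation under study day 1 only. The Feasibility analysis section promises a proportion and a one-sided 95% confidence interval for each criterion but does not say which denominator applies to this one.

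**The concern.** Sample size calls drug initiation one of the two most important feasibility measures, and criterion 3 is one of four conditions that must all hold. With randomized patients as the denominator, it measures how reliably the first dose follows allocation. With consented patients, it also absorbs every loss between consent and randomization.

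An infant consented in the pre-study column of Table 1 who is placed on ECMO, or receives more than one dose of stress ulcer prophylaxis before allocation, no longer meets the eligibility criteria in Table 2. That infant cannot receive a first dose of study drug but stays in the denominator in Outcomes.

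Two things are at stake. The trial could be called not feasible although drug initiation worked as planned. And if the two counts differ, whoever reports the result has to choose a denominator after seeing which one passes.

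**Working it through.** **Inputs.** From Sample size: n = 100 randomized, a one-sided 95% limit, a target of 80%, a stated minimum observed rate of 86.9%, and the companion statement for screening at n = 600, "as long as the observed screening rate is at least 82.7" per cent. From Outcomes: more than 80% of consented patients. The number consented but not randomized is not given, so it is an assumption here and is called k.

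**Step 1: reproduce the plan's figure.** The exact (Clopper-Pearson) one-sided 95% lower limit for x successes in n is the 5th percentile of a Beta(x, n − x + 1) distribution. Setting it equal to 0.80 and solving for x/n gives:

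- n = 100: 86.89% (stated 86.9%)
- n = 600: 82.74% (stated 82.7%)

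Both stated figures reproduce. In whole patients, 87/100 has a lower limit of 80.1% and 86/100 has 79.0%, so 87 of 100 randomized is the smallest count that meets the sizing rule.

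**Step 2: change only the denominator.** Keep 87 infants dosed on time out of 100 randomized, and let the number consented be 100 + k. The rate in Outcomes is then 87/(100 + k).

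| k (assumed) | Rate | Exact one-sided 95% lower limit |
|---|---|---|
| 0 | 87/100 = 87.0% | 80.1% |
| 1 | 87/101 = 86.1% | 79.2% |
| 5 | 87/105 = 82.9% | 75.7% |
| 8 | 87/108 = 80.6% | 73.2% |
| 9 | 87/109 = 79.8% | 72.5% |
| 20 | 87/120 = 72.5% | 65.0% |

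**Step 3: read the table against each rule separately.** The two sections also use different pass rules. Sample size wants the lower confidence limit to reach 80%. Outcomes, as worded, compares the observed proportion with 80%.

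- Lower-limit rule: k = 1 is enough to miss it.
- Observed-proportion rule: k = 8 still passes and k = 9 fails.

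Drug initiation among randomized infants is the same in every row.

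**Step 4: the ceiling.** If all 100 randomized infants were dosed on time, the rate in Outcomes could not exceed 100/(100 + k). At k = 20 this is 83.3%, with a lower limit of 76.7%. At k = 25 it is exactly 80.0%, which is not more than 80%.

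**The case against.** The strongest reply is that the authors mean the same 100 infants throughout. The article plans to enroll 100, treats consent as the point of enrollment, and has 100 to be randomized. Nowhere does it plan for consented infants who are not randomized. If every consented infant is randomized, k = 0 and the two definitions coincide. This stands as a limit on the size of the problem. It does not remove the contradiction, because the list in Outcomes uses randomized for criterion 2 and consented for criterion 3.

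A reader might infer more than the documents support:

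- **Consent before birth or before admission.** The plan to "send mailers to eligible patients prior to delivery or surgery" suggests it, but mailers are awareness material, listed alongside staff education and posted signs. Investigators approach families of eligible patients, and admission to the cardiac ICU is an inclusion criterion. Table 1 allows consent before study day 1 and says no more than that.
- **Infants who turn out not to need 24 h of support.** Eligibility rests on anticipated support, so such an infant can still be randomized and is not an example of the loss.
- **The unstated start of the 48 h.** An article may leave this to the full protocol, so its absence is not a finding in itself. It is worth settling in the same sentence as the denominator.

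It can also be said that a consented denominator is a legitimate, stricter measure of the path from consent to dose, and that changing Sample size instead would also remove the conflict. That is fair. The randomized denominator is preferred because the existing precision calculation was built on it and then needs no rework.

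**Conclusion.** The point holds as an inconsistency between the sizing and the decision rule of one go/no-go criterion. The 86.9% figure is correct for 100 randomized patients. It and the accompanying confidence statement do not carry over to a consented denominator.

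The practical effect depends on a count the article does not give, and may be nil. Starting from 87 of 100 dosed on time, one consented but unrandomized infant misses the Sample size threshold and nine miss the Outcomes rule. Both counts are illustrations. They are tied to that starting point and should be quoted with the rule each belongs to, because a pass on the Outcomes rule alone begins at 81/100.

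Nothing here touches randomization, the safety comparison or the microbiome analysis. Severity: should fix.

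**What to change.** In Outcomes, restate criterion 3 as the proportion of randomized patients who receive the first dose of study drug within 48 h of randomization, so that it matches Sample size. Report the number and share of consented infants who were not randomized as a separate descriptive item. A new item is needed because criterion 2 is randomized over eligible and does not count consents. On the article's own expectation of 200 eligible and 100 randomized it sits at 100/200 = 50% against a 20% threshold, so it would hardly register this loss.

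The cost is one sentence in the outcome definition and one extra line in the results. The times of randomization and first dose are ones a blinded drug trial normally holds. The sizing stays at n = 100, with 87 needed. The downside is that criterion 3 no longer reflects loss between consent and randomization, which would be visible only in the descriptive item.

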### Statistics

The study will be double-blinded, and we will utilize an intention-to-treat (primary analysis) and per protocol (secondary) analysis. Trial participants who do not complete the intervention will remain in the primary, intention-to-treat analysis of trial outcomes. Data will be reviewed every 6 months by the DSMB. Homogeneity of the two treatment arms will be assessed using a Fisher exact or chi-square test for categorical variables and a Student *t* test (parametric) or Wilcoxon rank sum test (non-parametric) for continuous variables.

#### Feasibility analysis

For each feasibility outcome measure, we will report the proportions of screened patients and/or participants meeting each criterion successfully and the associated one-sided 95% confidence interval.

#### Safety analysis

A two-sided 95% confidence interval will be constructed for treatment difference in the proportion of patients with UGI bleeding and hospital-acquired infections, as well as for each treatment-arm specific rate of UGI bleeding.

#### Microbiome analysis

Once the rRNA sequencing is completed, we will perform taxonomic profiling to identify distinct microbial lineages and then compare them to the published Greengenes, SILVA (for 16S), and UNITE (for ITS1) Reference Database [18–20]. The primary characteristics to be assessed between treatment arms are as follows: (a) within-sample and between-sample overall ecology of the microbial community, (b) absolute and relative abundance of microbial communities, and (c) pattern classification analysis to identify diversity [21]. We will then perform per-feature multivariable association analyses that estimate which microbiome attributes differ by treatment arm as well as between time points, while accounting for covariates, to identify how microbes are affected by outcomes in the presence of certain covariates [22–24]. We will adjust for delivery type (C-section vs. vaginal delivery), nutrition type (breast milk vs. formula), and antibiotics prescribed to the patient (not mother) as these are known confounders in the infant gut microbiome.

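### The microbiome plan gives no detection limit for the between-arm difference in change and does not list the infant's own initiation sample as a covariate; adjusting for it would sharpen a valid comparison at little cost

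*Protocol article*

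**What the plan says.** All references are to the protocol article.

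- **Outcomes.** The gut microbiota are to be explored by "comparing the absolute and serial differences in the abundance of bacteria and functional microbial profiles between those receiving SUP compared to placebo". Both the level and the change over time are thus compared between arms.
- **Sample size, microbiota paragraph.** There are 600 samples from 100 patients, two per site. Detectable levels at power 0.9 are 1.36% (rare taxa) and 3.46% (common taxa), stated once for two contrasts: "within a treatment arm between two time points, and similarly between two treatment arms at a given time point". The covariates assumed there are antibiotics, age and hospital-acquired infections.
- **Microbiome analysis.** One sentence begins "The primary characteristics to be assessed between treatment arms are as follows". The next says that per-feature models will "estimate which microbiome attributes differ by treatment arm as well as between time points, while accounting for covariates". The adjustment set follows: "We will adjust for delivery type (C-section vs. vaginal delivery), nutrition type (breast milk vs. formula), and antibiotics prescribed to the patient" (the patient's, not the mother's).
- **Measurements and definitions.** Oral swabs, gastric aspirates and discarded blood are taken along with "urine at the initiation and conclusion of the study". Stool is collected serially.

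**The concern.** Three parts of the plan do not line up. The outcome includes a between-arm difference in change. The detection limits cover a within-arm change and a single-time-point arm comparison, but not that difference. The analysis names an arm effect and a time effect; neither covariate list contains the infant's starting value, and no arm-by-time contrast is named.

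Two things are at stake. The first is precision: an infant's starting microbiota may well predict the end sample, and leaving it out leaves that variation in the error term. The second is interpretation. Feeds and antibiotics, which the article itself calls known confounders of the infant gut microbiome, can change during an ICU stay in both arms. A shift within the H2RA arm is therefore expected to some degree whatever the drug does, and it does not isolate the drug's effect.

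**Working it through.** **Inputs from the article.** 100 patients allocated 1:1, so about 50 per arm; three sites with two samples each; power 0.9; a Bonferroni-adjusted 0.05. The sample count reproduces: 100 × 3 × 2 = 600.

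**What cannot be reproduced.** The limits of 1.36% and 3.46% need the taxon variances, the number of taxa tested and the correlation between an infant's two samples. The article gives none of these.

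**Assumptions.** One feature on a scale with SD 1, a normal approximation, two-sided alpha 0.05, correlation ρ between the initiation and end samples of 0.3 to 0.7, and an initiation sample not yet affected by study drug.

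**Step 1. Standard error of each between-arm contrast, 50 per arm.**

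- End sample, unadjusted: √(2/50) = 0.200
- End sample, adjusted for baseline: 0.200 × √(1 − ρ²) = 0.191, 0.173, 0.143 for ρ = 0.3, 0.5, 0.7
- Change score: 0.200 × √(2(1 − ρ)) = 0.237, 0.200, 0.155

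**Step 2. Power for a 0.6 SD effect, ρ = 0.5.**

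- Unadjusted: Φ(0.6/0.200 − 1.96) = Φ(1.04) = 85%
- Adjusted: Φ(0.6/0.173 − 1.96) = Φ(1.50) = 93%

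**Step 3. An effect with exactly 90% unadjusted power.** This is d = (1.960 + 1.282) × 0.200 = 0.648 SD.

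| ρ | End sample, unadjusted | End sample, baseline-adjusted | Between-arm change |
|---|---|---|---|
| 0.3 | 90% | 92.5% | 78% |
| 0.5 | 90% | 96.3% | 90% |
| 0.7 | 90% | 99.5% | 99% |

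Adjustment multiplies the variance by 1 − ρ² = 0.91, 0.75, 0.51. That is worth an unadjusted trial of 50/0.91 = 55, 50/0.75 = 67 or 50/0.51 = 98 per arm. At ρ = 0 nothing is gained. The factor √(1 − ρ²) on the detectable effect does not depend on alpha, so the relative gain survives Bonferroni correction. With 250 tests as an illustration, the detectable effect falls from 1.00 SD to 0.95, 0.87 or 0.71 SD.

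**Step 4. Validity of the between-arm tests.** In 20,000 simulated trials per ρ, with no drug effect and a 0.5 SD time shift in both arms, the end-sample arm comparison rejected in 4.8% to 5.1% of trials and the between-arm change in 4.7% to 5.2%. Both hold their level.

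**Step 5. What the within-arm contrast responds to.** Its standard error is √(2(1 − ρ)/50). In the setting of Step 4 it rejects with probability 85%, 94% and 99.5% for ρ = 0.3, 0.5, 0.7 (at alpha 0.05/250: 23%, 43%, 80%). These figures are power to detect the assumed drift. They show only that a significant within-arm change carries no information specific to H2RA. Conversely, a drug effect of −0.5 SD that offsets a drift of +0.5 SD leaves this test rejecting in 5% of trials, while the baseline-adjusted arm comparison has 74% to 93% power.

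**The case against.** A reader might infer more than the article supports, in three ways.

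- **That H2RA is never tested against placebo.** This is wrong. The Abstract, Sample size, Measurements and definitions, Outcomes and Microbiome analysis sections each plan a between-arm comparison, and the serial differences in Outcomes express a between-arm contrast of change in words.
- **That type I error is inflated.** It is not. The within-arm null is no change over time; rejecting it when drift exists is correct. Nowhere does the article say that a within-arm shift will be read as a drug effect.
- **That the estimated drug effect is halved.** That would need one arm effect pooled over the initiation and end samples. The article states no such model, and its power statement for arms at a single time point points away from it.

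Beyond that, the defence can say that the exact model may sit in an analysis plan not shown, that an unadjusted end-sample comparison is valid under randomisation, and that this is an exploratory secondary outcome of a feasibility pilot. All of this stands, and it sets the weight of the point. It does not remove the point: the article has itself named the contrasts with detection limits and listed the adjustment variables, and neither matches its own outcome definition as well as it could.

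**Conclusion.** The point holds as an improvement in precision and a matter of alignment, not as the correction of an invalid test. Adding the initiation sample to the between-arm model raises power from about 85% to about 93% (0.6 SD, ρ = 0.5), or from 90% to between 92.5% and 99.5% (0.648 SD, ρ = 0.3 to 0.7). Effect sizes, correlations and time shifts are assumptions, not document figures. For sparse taxa with weak correlation between samples the gain would be small.

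The within-arm contrast is legitimate as description but cannot by itself support a treatment claim. The detection limit that readers need, for the between-arm contrast the outcome calls for, is not given.

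**What to change.** **Microbiome analysis.** For each feature, define the inferential test as the H2RA-placebo difference at the end-of-treatment sample, adjusted for the same infant's initiation value in addition to the listed covariates. For serial stool, use the arm-by-time contrast with a random effect per infant, preferably with a common baseline mean for the two arms. With one initiation and one end sample and no such constraint, it reduces to the change-score comparison, which at ρ = 0.3 has less power than the unadjusted end sample (78% against 90%). Label within-arm change descriptive.

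**Sample size.** State the detection limit for that between-arm contrast, with the assumed correlation and number of features. Do not rest the treatment question on the within-arm limit.

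**Cost.** A few sentences of analysis text and a rerun of the detection limits; no new samples. Infants without an initiation sample need a mixed model or a missing-indicator term. This should be settled in advance, since the Discussion already expects scant gastric fluid and irregular stools. The plan should also confirm that the initiation sample precedes the first dose: the schedule in Table 1 places both on study day 1 without giving their order.
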